#### Observational studies of multivitamin and folic acid use and clefts

Several case–control observational studies have reported a protective effect of periconceptional use of multivitamins and folic acid on occurrence of clefts [see Botto et al.
[78] for a review]. The estimated decrease in CL/P risk with supplements containing folic acid has ranged from 18%
[79] to 50%
[80,81]. Studies of multivitamin use without specification of folic acid content have reported risk reductions of 30%
[82], 40%
[83,84], and 50%
[85]. The smaller risk reductions were generally not statistically significant. Only one observational study
[86] has reported an increased risk for CL/P with folic acid supplements (by 30% but insignificant) yet their control group included only children with birth defects outside of midline defects, which might be interpreted as a protective severity reduction effect of folic acid for those anomalies.

Other studies of micronutrient and folate exposures have also suggested associations with oral clefts in humans. Dietary folate intake was reported to be associated with oral cleft risk by up to 70% increase with 0.18mg compared to 0.35mg of daily folate intake
[87]. Low maternal B6
[10] measured after pregnancy was reported to increase the risk of CL/P, particularly in cases with low serum folate. Post pregnancy low B12 levels and low infant serum folate have also been linked to increased oral cleft risk
[81]. B1 and B6 deficiencies in maternal diet were also associated with an increased risk of oral clefts
[88] as were myo-inositol and zinc
[89,90].

Exposure to folic acid antagonists such as antiepileptic drugs and dihydrofolate reductase inhibitors was reported to double the odds for oral clefts
[91]. Animal studies also provide support for anti-teratogenic effects of prenatal folic acid supplementation and dietary folate. Peer et al.
[92] showed a 69% reduction in cortisone induced cleft palate occurrence in mice with folic acid injection; there was an 82% reduction with a combined treatment of folic acid and B6. Folic acid supplementation was also shown to decrease the frequency of retinoic acid induced cleft palate in mice by up to 92%, with suggested additive effects with methionine
[93]. Procarbazine induced cleft palate was also reported to decrease with folic acid supplementation in rats

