#### Secondary hypotheses

The following secondary hypotheses will be evaluated:

An increase in serum and/or red cell folate levels in all women following daily supplementation with folic acid.

When compared to the 0.4 mg supplemented groups, the 4 mg per day group will have the following:

‐Greater increases in serum and/or red cell folate.

‐Decreases in the recurrence of NSCL/P in each of the following subgroups:

•Women with NSCL/P themselves

•Women with one or more children with NSCL/P

‐A decrease in the severity of NSCL/P in offspring of trial mothers.

‐No increase in twinning rates.

No increase in miscarriage rates.

No increase in rates of preeclampsia.

‐No increase in rates of other birth defects.

‐No decrease in birth weight

‐No decrease in gestational age

A decrease in recurrence of NSCL/P in the group of study subjects compared to an historical control group obtained from the populations served by the craniofacial clinics participating in the study.

A greater decrease in the recurrence of NSCL/P in the group of study subjects receiving 4 mg of folic acid when compared to the historical control group relative to that of the group receiving 0.4 mg when compared to the same control group.

Under separate funding we will examine the role of genes involved in folate metabolism on folate, B12 and homocysteine levels, as well as potential interaction between these genes and the supplementation dose. This project will also establish a resource to examine the long-term outcomes of infants exposed to high dose folic acid in utero.

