#### Historical control group

The recurrence rates in this study will be compared to that of an historical control group. The rationale for using this group relates to the inability to use a placebo control in this study due to ethical considerations. A comparison with an historical control group will allow the assessment of the combined effect of a minimum dose of folic acid of 0.4 mg and a maximum dose of 4 mg by comparing the NSCL/P recurrence rate in the total study group to that of a group of women who did not receive the folic acid dose of 0.4 mg per day. The effect of each of the two folic acid doses on the recurrence risk of NSCL/P could also be evaluated by comparing the NSCL/P rate in each of the two study groups (0.4 mg and 4 mg folic acid) to that of the historical control group.

The historical control will include women with NSCL/P or mothers of children with NSCL/P who are registered at the craniofacial clinics enrolled in the study. Those clinics have been involved in the provision of services to subjects with clefts for an extensive period, thus rates of cleft recurrence can be calculated over an extended time course providing not only cross-sectional data but also trends data adding to the validity of the historical control approach. Such data will reveal any changes in recurrence rates that might have occurred over time.

Taking into consideration the traditional internal validity challenges associated with using historical controls, no major historical events that could affect recurrence rates of NSCL/P in this population are expected to have occurred during the years immediately preceding this study.

Since the two randomized study groups (0.4 mg and 4 mg folic acid) will be compared to the same group of historical controls, any differences in the relative decreases of NSCL/P recurrence rates that may be observed between each of the study groups and the historical control group can be safely attributed to the effect of administered folic acid.

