##### Exclusion criteria

1. Having a first degree relative (that is a parent, sibling or child) who has cleft palate only.

2. Cases resulting from consanguineous couples (first, second, and third degree, i.e., first cousins or closer).

3. Couples where at least one of the two is definitely sterilized.

4. Women who are using intrauterine devices

5. Women who are using injectible contraceptives

6. Women on anti-epileptic drugs (The metabolism of anti-epileptic drugs requires a great deal of folic acid. Therefore, it is very difficult to verify the effect of folic acid on the prevention of clefting among these women. In order to avoid this situation, such women will not be included in this study).

7. Women on drugs that contain benzodiazepines

8. Women who are pregnant. They will be re-contacted later at an appropriate time for participation in the study.

9. Women who are planning to move outside of the catchment area of the study within the next year.

10. Women who have B12 deficiency (B12 level is below 174 pg/ml or 134.328 pmol/L).

11. Women who are allergic to folic acid.

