#### Sampling, recruitment, and screening procedures

##### Sampling

Potential study subjects include a convenience sample of women with NSCL/P and/or mothers of at least one child with NSCL/P who currently attend or have attended in the past the study clinics for their own care or for the care of their children during the study period and who meet the inclusion criteria (age and residence) listed above. Potential subjects will be invited to participate. The majority of potential subjects (about 70%) are expected to be mothers of children with NSCL/P and the rest (30%) to be women who themselves have NSCL/P. Based on published literature and review of CL/P pedigrees at HRAC clinic in Bauru, the recurrence rates in the two subject groups of women with NSCL/P and mothers to a child with NSCL/P were estimated to be about 7 and 4 percent respectively.

While women up to 45 years of age are potentially eligible to participate, the sampling frame will be limited, when possible (e.g. when women’s age is known a priori from the clinic’s records), to women who are up to 40 years of age. The rationale for this sampling frame is that chances of pregnancy and propensities to have children decrease significantly after 40 years of age. Yet, due to potential inaccuracies in the age of women in the clinic’s records used for sampling, women who are invited to participate in the study and who are between 40 and 45 years of age will still be eligible to participate in the study on age basis in order to keep a positive environment for implementation of the study in the local community.

All potential subjects are identified from the clinics’ medical records and registries in addition to active surveillance of all patients who attend the clinics for care. The study staff will search patient records to identify potentially eligible subjects based on the primary information that are available in these records including CL/P diagnosis, women’s age, and residence. All patient charts from the past 10 years will be reviewed to identify women who themselves or their children have been treated at the clinic. Study staff will search the records of subjects who will attend the clinic to also identify potential subjects on a weekly basis. The study will be promoted to all the staff of these craniofacial clinics so that they also can assist in identifying and referring subjects to the study and will be advertised in local media.

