#### Power analysis

Table
8 presents estimates of prospective number of births in the two study groups required for 70 and 80% statistical power and 30, 50, and 70% reductions in CL/P recurrence for alternative recurrence rates of 3, 5, and 7% in the 0.4 mg group. The 30% reduction represents a lower effect that is still very clinically significant, while the 70% represents an effect similar to that observed for NTD recurrence
[118]. The recurrence rates cover most of those reported in the literature and we use the 5% rate as a primary reference for our total suggested sample size given that it represents a proportional estimate of the 4 and 7% recurrence rates assuming that 30% of the study subjects will be women with clefts and 70% will be mothers to children with clefts. The power calculations are based on a Type I error probability of 5%. We use a one sided test as the recurrence rate in the 4 mg is not expected to exceed that of the 0.4 mg group given the converging evidence of protective effects of folic acid; a Fisher’s exact test is used.

**Table 8 T8:** Power analysis for primary hypothesis

**Baseline recurrence rate**	**% Reduction**	**Power**	**Total births**	**Total subject years**
*0.07*	70	0.8	524	5475
		0.7	418	4368
	50	0.8	1114	11641
		0.7	874	9133
	30	0.8	3324	34734
		0.7	2574	26897
*0.05*	70	0.8	742	7753
		0.7	590	6165
	50	0.8	1582	16531
		0.7	1240	12957
	30	0.8	4734	49467
		0.7	3666	38307
*0.03*	70	0.8	1254	13103
		0.7	996	10408
	50	0.8	2676	27962
		0.7	2096	21902
	30	0.8	8024	83845
		0.7	6210	64890

For a 50% reduction in a baseline rate of 5% recurrence, a total of 1582 births distributed equally across the two treatment groups are required. This number of births also provides acceptable power (0.75) to detect a 60% decrease in a 3% baseline recurrence rate, or a 40% decrease in a 7% baseline risk. If the 4 mg dose shows a preventive effect similar to that seen for NTDs (70%), the required numbers of births are halved regardless of the baseline recurrence risk (range from 524 to 1254 births for 80% power). The numbers of births required to observe a 30% reduction are about three times as large those for a 50% reduction.

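### The historical control group is compared with the trial without any stated restriction to trial eligibility or control for risk-group mix, so part of an apparent folic acid effect could be case mix

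*Protocol article*

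**What the plan says.** **The comparator.** In Historical control group: "The historical control will include women with NSCL/P or mothers of children with NSCL/P who are registered at the craniofacial clinics". The section also describes these women as not having received 0.4 mg of folic acid daily. Secondary hypotheses adds only the source: a "historical control group obtained from the populations served by the craniofacial clinics participating in the study".

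**The comparisons.** One listed secondary hypothesis is "A decrease in recurrence of NSCL/P in the group of study subjects compared to an historical control group". A second asks whether the fall against that group is greater with 4 mg than with 0.4 mg. The Abstract and the Design section both say that the total sample and each dose group will be compared with the historical rate.

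**The trial sample.** Inclusion criteria set age 16 to 45 and residence in the catchment area. Exclusion criteria remove, among others, consanguineous cases, women on anti-epileptic drugs or benzodiazepines, and any woman "Having a first degree relative (that is a parent, sibling or child) who has cleft palate only".

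**The risk groups.** In Sampling, recurrence rates for affected women and for mothers of an affected child "were estimated to be about 7 and 4 percent respectively". The Power analysis takes its 5% baseline from these, "assuming that 30% of the study subjects will be women with clefts and 70% will be mothers to children with clefts".

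**The defence of the comparator.** It concerns time only: trend data from the clinics, and no major event expected in the preceding years. It does not address eligibility or case mix. The covariate adjustment in the Analysis plan is aimed at imbalance between the two randomised groups.

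**The concern.** A historical comparison needs the two groups to be alike in everything that drives recurrence except folic acid. On the protocol's own figures, risk group is a strong driver: 7% against 4%. Nothing in the text makes the share of affected women among historical births equal to the share among trial births. The trial's eligibility limits are not stated for the historical group either, and the protocol itself treats some of them as related to cleft risk. On anti-epileptics, for example, it says: "Exposure to folic acid antagonists such as antiepileptic drugs and dihydrofolate reductase inhibitors was reported to double the odds for oral clefts".

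This is separate from drift over time. It would bias the comparison even if background recurrence had been constant for decades.

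There is no placebo arm, so this comparison is the only evidence the trial offers on whether 0.4 mg, or folic acid at either dose, lowers recurrence. A difference in case mix would be read as a folic acid effect, or could hide one.

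**Working it through.** **Inputs**
- Recurrence 7% in affected women and 4% in mothers of an affected child (Sampling).
- Trial mix 30% affected women, 70% mothers (Sampling; Power analysis).
- 1,582 trial births (Power analysis).
- Share *w* of affected women among historical births: not in the documents, so a range is shown.
- Number of historical births: not in the documents; 5,000 is assumed where one is needed.

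**Step 1. The plan's own figures.** Trial rate without any dose effect = 0.3 × 7% + 0.7 × 4% = 2.1% + 2.8% = 4.9%, which the protocol rounds to 5%. The 1,582 births also reproduce: 5% against 2.5%, one-sided 5%, 80% power, normal approximation with continuity correction gives 792 per arm, 1,584 in total. That calculation concerns the randomised comparison and is not in question.

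**Step 2. Historical rate as a function of mix.** Rate(*w*) = 7% × *w* + 4% × (1 − *w*). Apparent change with no folic acid effect = (4.9% − Rate) / Rate.

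| Assumed *w* | Historical rate | Apparent change in the trial |
|---|---|---|
| 10% | 4.3% | +14.0% |
| 20% | 4.6% | +6.5% |
| 30% | 4.9% | 0.0% |
| 40% | 5.2% | -5.8% |
| 50% | 5.5% | -10.9% |

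**Step 3. Effect on a test.** Assume 5,000 historical births and a one-sided 5% test of two proportions (the protocol fixes neither for this comparison). The chance of a false significant decrease is Φ((d − 1.645 × SE0) / SE1), where d is the historical rate minus 4.9%, SE0 is the pooled standard error and SE1 the unpooled one.
- At *w* = 40%: d = 0.003, SE0 = 0.00636, SE1 = 0.00627, so Φ(−1.19) = about 12%, against a nominal 5%.
- At *w* = 50%: about 23%.
- At *w* = 20%, the mirror-image test for an increase is falsely positive about 13% of the time; at *w* = 10%, about 27%.

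**Step 4. Which comparisons are exposed.** Write R4, R0.4 and RH for the three rates. The total-group and per-dose comparisons contain RH once, so any bias in RH passes straight through. The hypothesis of a greater fall with 4 mg uses RH twice: (RH − R4) − (RH − R0.4) = R0.4 − R4, and on the ratio scale (R4/RH) / (R0.4/RH) = R4/R0.4. RH drops out and the randomised contrast remains.

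**Step 5. The remaining eligibility limits.** The documents give neither the prevalence nor the recurrence effect of consanguinity, drug use, maternal age or a relative with cleft palate only among registered women. Their contribution cannot be computed.

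**The case against.** The strongest reply has four parts.

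**The text is silent; it does not waive the criteria.** A reader might infer that the controls are all registered women, with the trial's exclusions deliberately dropped. The protocol says neither. This is a condensed article, and finer detail on control eligibility may sit in a fuller document. That is fair, and the point is limited accordingly. But the article does choose the comparator, states the rate comparisons and argues for their validity, and that argument covers only time. A better specified comparison is available at little cost.

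**The same clinics should give a similar mix.** The 30/70 expectation is for potential subjects drawn from these clinics, so the best document-based guess for the historical group is also near 30/70, with little bias. This largely stands. It is why 20% to 40% is the main range, and why a share as high as 60% (5.8%, an apparent fall of about 16%) should not be used as a headline. It does not settle the matter. The 30/70 figure describes women invited, not births. The Analysis plan itself treats who continues and who gives birth as non-random. The trial's site mix follows recruitment targets, with 2,248 of 5,368 new enrollees (42%) at Bauru, while the historical group covers an extended period.

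**Drug exposure is partly dealt with.** A reader might add an inflation of the historical rate for anti-epileptic use. The protocol's definition of NSCL/P already removes cases exposed in utero to phenytoin or valproic acid, and presumably applies to historical cases too. No exposure prevalence is given, and the reported doubling of odds is for oral clefts generally, not for recurrence. No figure for this is supportable.

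**Comparing total rates does not rule out risk-group analysis.** In the Historical control group section, the total study group means the two doses pooled. The protocol plans separate risk-group analyses elsewhere. Those are written for the randomised arms, however, and nothing extends them to the historical comparison.

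**Conclusion.** The point holds in a limited form. As written, the trial-versus-historical comparisons carry no stated restriction to trial eligibility and no stated control for risk-group mix, so they can be biased in either direction. This affects one listed secondary hypothesis (all study subjects against historical controls) and the per-dose comparisons announced in the Abstract and Design.

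A reader might infer that both historical hypotheses fail, or that the trial's main result is in doubt. Neither follows: the randomised 4 mg versus 0.4 mg comparison does not use the historical group, and the shared control largely cancels from the contrast of the two doses.

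On the protocol's own 7%, 4% and 30/70, the bias from risk-group mix is about +6.5% to -5.8% if affected women make up 20% to 40% of historical births, and about +14% or -11% at 10% or 50%. These shares are assumptions. If the mixes happen to match, this part of the bias is zero. The part due to the other eligibility limits is of unknown size. The change should be made, but it concerns secondary evidence only.

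**What to change.** State in the protocol that historical births count only if they meet the trial criteria that charts can verify: the NSCL/P case definition, maternal age 16 to 45, the catchment area, no consanguinity, no first-degree relative with cleft palate only, and no recorded anti-epileptic or benzodiazepine use where drug records exist.

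Replace the comparison of crude rates with one made within risk group, or standardise the historical rate to the trial's observed risk-group and site mix of births. With a 30/70 trial mix, standardising on risk group brings the expected historical rate back to 0.3 × 7% + 0.7 × 4% = 4.9% and removes the risk-mix bias whatever the registry's own mix.

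The cost is a smaller historical cohort, slightly wider intervals and some extra abstraction. The planned review of ten years of charts is meant to find trial subjects, so abstracting historical births is additional work. Drug use will be recorded incompletely, and that limit should be reported with the result.

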Upon delivery, the Clinical Coordinator will follow with the subject and her physician to check on the occurrence of NSCL/P and other birth defects in the infant. Research staff may also access prenatal care records of subjects, pending approval of subject prenatal care providers, to abstract significant health and care events that occurred during pregnancy and that required physician care.

The Clinical Coordinator or Co-Prinicipal Investigator will also evaluate in person the infant for the presence clefting and other anomalies either through an appointment at the clinic or at subject’s home as convenient to the subject. When a birth defect is identified, research team members will carry out a complete physical exam and confirm all oral cleft diagnoses. The Co-Principal Investigator may also evaluate the infant along with the Clinical Coordinator or independently.

Gestational loss will be reviewed by one of the research team members (Clinical Coordinator, Co-Principal Investigator, and/or geneticists of the clinic). When available, miscarriage material will be examined. This examination will may include macroscopic analysis (presence or absence of NSCL/P; other apparent malformations), photographic documentation, and cytogenetic analysis in the event of malformations depending on the capacity of the clinic site in doing these investigations.

After completion of a pregnancy outcome, subjects will be asked about their willingness to resume participation in the study at an appropriate time following the end of pregnancy. Subjects who are willing to resume participation will be assigned to the same treatment group as their previous randomization assignment, and the standard enrollment procedures will be followed.

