#### Description of biological measures

The following laboratory measures will be collected from the subjects found in Table
3.

**Table 3 T3:** Laboratory measures

**Laboratory measure**	**Timing**	**Aim**	**Performed by**
Complete blood count	At baseline, every 12 months post initiation of supplementation, and at pregnancy confirmation.	Anemia	Laboratory of study clinic
Pregnancy test	Whenever menstrual delay of 14 days or more is detected	Pregnancy	Laboratory of study clinic or an outside affiliated laboratory
Folate analysis	At baseline, every 12 months post initiation of supplementation, and at pregnancy confirmation.	Measure serum/red cell folate concentration	Laboratory of study clinic or an outside affiliated laboratory
Vitamin B12 analysis	At baseline and every 12 months thereafter	Detect pernicious anemia	Laboratory of study clinic or an outside affiliated laboratory

The following physical exam measures of babies born to subjects will be abstracted from medical records:

Birth defects

Birth weight

Length

Head circumference (when available)

The Clinical Coordinator will also obtain and document information on the presence of craniofacial malformations including clefts or other birth defects in babies born through personal evaluation of the infant, contact with the subject’s doctor after delivery, or abstraction from the medical record of the infant, but the clinical coordinator will make every attempt to evaluate in person every infant born into the study. Information about any malformations detected during the prenatal period through ultrasound testing will also be obtained from contact with the subject, her prenatal care provider, or through abstraction from the prenatal care record.

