#### Primary and secondary outcome measures

##### Primary outcome measure

The primary outcome assessed is a measure of recurrences of NSCL/P in offspring of the trial mothers. All live born children born of at least 500g or gestation of 24 weeks or beyond with NSCL/P (only Tessier X clefts included) will be identified by case finding and verified by in person clinical exam. For the classification of cleft lip and cleft palate malformations, the following schemata taken from the Division of Plastic Surgery and Burns of the Department of Surgery of the University of Sao Paulo Medical School, Brazil will be used in Table
6.

**Table 6 T6:** Classification of cleft lip and cleft palate malformations:

**Group I**	**Pre-incisor foramen clefts (Clefts lying anterior to the incisor foramen). Clefts of the lip with or without an alveolar cleft.**	
	a) Unilateral	
	Right	Total – when they reach the alveolar arcade
	b) Bilateral	Partial
		1) Total}On one or both sides
		2) Partial
	c) Median	1) Total
		2) Partial
Group II.	Trans – incisor foramen clefts (Clefts of the lip, alveolus and palate)	
	a) Unilateral	Right
		Left
	b) Bilateral	
Group III.	Post-incisor foramen clefts (Clefts lying posterior to the incisor foramen)	
	1) Total	
	2) Partial	
Group IV.	Rare facial clefts	

*Taken from Division of Plastic Surgery and Burns of the Department of Surgery of the University of Sao Paulo Medical School, Brazil (Spina* et al.*, 1972).*

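### The historical recurrence rate comes from clinic-registered women with no like-for-like counting of later births, so differential capture could produce or mask a decrease against it

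*Protocol article*

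**What the plan says.** The Historical control group section of the protocol article defines the comparison group as "women with NSCL/P or mothers of children with NSCL/P who are registered at the craniofacial clinics enrolled in the study". Because the clinics have treated cleft patients for a long time, it concludes: "thus rates of cleft recurrence can be calculated over an extended time course providing not only cross-sectional data but also trends data". It presents this as support for the validity of using historical controls and adds: "Such data will reveal any changes in recurrence rates that might have occurred over time". It acknowledges that historical controls have internal validity problems, but the only one it discusses is outside events: "no major historical events that could affect recurrence rates of NSCL/P in this population are expected". It does not say how later births to registered women are found or counted.

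Under Secondary hypotheses, one stated hypothesis is "A decrease in recurrence of NSCL/P in the group of study subjects compared to an historical control group". The Historical control group section also says that each dose group could be compared with the historical rate.

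Trial births are captured differently. Women are contacted every two months. Under Follow-up of study subjects, staff "will also evaluate in person the infant for the presence clefting and other anomalies", and Table 5 schedules this within 60 days of delivery. Under Primary outcome measure, affected live births above the weight or gestation threshold "will be identified by case finding and verified by in person clinical exam". Under Description of biological measures, "the clinical coordinator will make every attempt to evaluate in person every infant born into the study", with the doctor's report or the medical record also accepted as sources.

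**The concern.** A recurrence rate needs a numerator (affected later births) and a denominator (all later births). A treatment clinic's long experience with cleft patients bears mainly on the numerator. A later child with a cleft brings the family back for care; an unaffected sibling need not appear in the records. The trial counts births prospectively, whatever the outcome. If the historical source records the two kinds of birth with different completeness, its rate is not comparable with the trial rate, and a difference can appear with no drug effect.

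Trend data do not settle this. A bias that is the same in every calendar period leaves no trend to see. A change in record-keeping or registration practice could look like a change in recurrence.

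At stake is the conclusion that folic acid at either dose lowers recurrence. The protocol uses the historical group for that purpose because a placebo arm was ruled out on ethical grounds, and the abstract announces the comparison.

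**Working it through.** **Inputs from the protocol article.** Planning recurrence is 7% for women with a cleft and 4% for mothers of an affected child, in an expected 30:70 mix (Sampling). Then 0.3 × 7% + 0.7 × 4% = 4.9%, which the Power analysis section uses as 5%. The total is 1,582 births with a one-sided 5% test.

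**The plan's own figure.** No rate, sample size or power is stated for the historical comparison. The primary sample size reproduces: 5% versus 2.5%, one-sided 5%, 80% power, with continuity correction, gives 792 per arm, or 1,584, against 1,582 stated. This point does not touch that figure.

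**Assumed inputs.** The documents give no capture rates. Let p be the true recurrence, the same in both periods (no drug effect), and u the capture of unaffected births relative to affected births in the historical source.

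Apparent historical rate: h = p / [p + (1 − p)u].

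Spurious reduction: 1 − p/h = (1 − p)(1 − u).

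With p = 0.05:

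| u | h | spurious reduction |
|---|---|---|
| 1.0 | 5.0% | 0 |
| 0.9 | 0.05/0.905 = 5.5% | 0.95 × 0.1 = 9.5% |
| 0.8 | 0.05/0.810 = 6.2% | 0.95 × 0.2 = 19% |
| 0.7 | 0.05/0.715 = 7.0% | 0.95 × 0.3 = 28.5% |

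The result depends little on p. At u = 0.8 the reduction is 19.2% for p = 4% and 18.6% for p = 7%.

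**The opposite direction.** If unaffected births are fully recorded but only a share a of affected births is, h = pa / [pa + (1 − p)]. For a = 0.9, 0.8 and 0.7 a true 5% reads as 4.5%, 4.0% and 3.6%. With no drug effect the trial rate would then appear about 11%, 24% and 41% higher than the historical rate, so a real decrease could be masked.

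**Chance of a false positive.** Take 1,582 trial births, a normal-approximation one-sided 5% test, and an assumed number of historical births. The chance of declaring a decrease when there is none is:

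| historical births (assumed) | u = 1.0 | u = 0.9 | u = 0.8 | u = 0.7 |
|---|---|---|---|---|
| 1,000 | 5% | 15% | 36% | 68% |
| 1,582 | 5% | 16% | 42% | 76% |
| 3,000 | 5% | 18% | 49% | 85% |

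More historical births make the false positive more likely, because the bias does not shrink with sample size.

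**What is not exposed.** The other historical hypothesis asks whether the 4 mg arm falls further below the historical rate than the 0.4 mg arm. On the absolute scale, (h − p4) − (h − p0.4) = p0.4 − p4, so h cancels. On the relative scale the difference is (p0.4 − p4)/h, so h changes its size but not its sign.

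**The case against.** The strongest reply is that the section defines the historical group by registered women, not registered children. A registered woman's unaffected children could be counted from her chart, a pedigree or an interview. The Sampling section shows that pedigrees exist at the Bauru clinic and were reviewed for recurrence. Abstraction rules of this kind commonly sit in a full protocol or manual rather than an article.

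Much of this stands. A reader might infer that siblings count only if they are themselves patients, or that some mothers with clefts are registered only through an affected child who is then counted as a recurrence. The text says neither. The inclusion criteria refer to women with clefts attending for their own care.

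A reader might also infer that the historical rate must be inflated. The documents do not establish a direction. The pilot reports high mobility (23% moved or not located, 18% untraceable), so affected later births could be lost too, and examining trial infants in person may raise detection in the trial.

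Nor do the documents support an extreme value such as u = 0.5, which would give 47.5%. They give no value of u, and the 50% design effect is the randomised dose contrast, not a historical one. At u = 0.5 a true 4% would read as 7.7%, whereas the planning figure for mothers of affected children, drawn from literature and the Bauru pedigrees, is about 4%.

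The reply does not rescue the section's positive claim. Pedigree review is cited for one clinic and for planning rates only. The Sampling section names diagnosis, age and residence as information in the records, not birth history. The section moves from long service to cleft patients straight to usable rates and trends that add validity, and that step does not follow without comparable capture of births.

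**Conclusion.** The point holds as a weakness in one non-randomised secondary comparison. The protocol does not ensure comparable capture of births before and during the trial, so a decrease from the historical rate in the total sample, and the size of each arm's decrease, could be produced or masked without any drug effect. The trends cannot validate the comparison.

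Direction and size are unknown. The 9.5% to 28.5% range rests entirely on assumed capture of 0.9 to 0.7 at 5% recurrence, and the sign reverses if affected births are under-recorded.

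A reader might infer that both historical hypotheses, or the trial's main result, are compromised. They are not. The randomised 4 mg versus 0.4 mg comparison does not use the historical rate, and the ordering of the two arms against a common historical rate is unaffected.

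**What to change.** In the Historical control group section, state that the historical rate is computed only from women with a complete recorded birth history, whether from a chart listing every live birth or by interview. Count only births after the qualifying event (the woman's own cleft, or her first affected child), exclude the index child, and apply the trial's live-birth and cleft definitions. Report the share of births with unknown status by calendar period, so that drift in completeness can be seen.

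If complete histories cannot be obtained, label the historical comparison and the trends descriptive, and delete the statement that trend data add to the validity of the historical control.

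The cost is fewer usable historical births, plus some abstraction or interview time. The task is familiar, since the enrolment form (FA03) already collects information on each trial woman's children. The descriptive fallback needs only a wording change.
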